## Abstract

**Background:**

New-onset neurological symptoms such as numbness and pain in lower extremities might appear immediately after conventional lumbar interbody fusion (LIF) surgery performed in patients with lumbar spinal stenosis.

**Methods and analysis:**

This is a multicenter, randomized, open-label, parallel-group, active-controlled trial investigating the clinical outcomes of modified LIF sequence versus conventional LIF sequence in treating patients with lumbar spinal stenosis. A total of 254 eligible patients will be enrolled and randomized in a 1:1 ratio to either modified LIF sequence or conventional LIF sequence group. The primary outcome measure is the perioperative incidence of new-onset lower extremity neurological symptoms, including new adverse events of pain, numbness, and foot drop of any severity. Important secondary endpoints include visual analogue scale (VAS) pain score and lumbar Japanese Orthopaedic Association (JOA) recovery rate. Other safety endpoints will also be evaluated. The safety set used for safety data analysis by the actual surgical treatment received and the full analysis set for baseline and efficacy data analyses according to the intent-to-treat principle will be established as the two analysis populations in the study.

**Conclusion:**

This study is designed to investigate the clinical outcomes of modified LIF sequences in patients with lumbar spinal stenosis. It aims to provide clinical evidence that the modified “fixation-fusion” sequence of LIF surgery is effective in treating lumbar spinal stenosis.

**Trial registration:**

http://www.chictr.org.cn/index.aspx ID: ChiCTR2100048507.

## Introduction

Lumbar spinal stenosis (LSS) may lead to severe pain in low back or leg and also neurogenic claudication [1]. In clinical practice, the lumbar interbody fusion (LIF) technique has been widely used in the treatment of LSS patients to restore the height of the intervertebral disc and foramen and also the sagittal volume of the lumbar spinal canal [2].

In recent years, however, the postoperative neurological symptoms after LIF surgery, characterized by new-onset postoperative pain or numbness, dysesthesia, and muscle weakness have aroused widespread concern among clinicians [3–7]. Although these symptoms are usually transient and would be significantly relieved by themselves, it has a great impact on the quality of life of patients at that time interval. Some researchers have hypothesized about what causes these symptoms. Postigo et al [8]reported an increased risk of numbness, pain, and even foot drop after over-distraction on LIF surgery. A study by Matsui et al [9]showed that during the process of nerve root being pulled, the nerve root usually has ischemia, and hence the traction pressure and duration may be the potential risk factors for nerve root injury. Fu et al [10] found that when the height of the intervertebral space was increased to 140% of the original height, the nerve root tension increased the risk of injury significantly.

These findings coincide with our clinical experience in recent prospective research [11]. In this prospective observational clinical trial, we observed that fixation followed by fusion implantation resulted in a more physiologic reconstruction of the intervertebral space height, rather than excessive distraction resulting in excessive tension of the walking nerve roots, and reduced the incidence of postoperative neurological symptoms. It is essential to acknowledge that previous studies have concluded that additional fusion in conjunction with decompressive surgery may not yield discernible benefits, furthermore, they have noted potential drawbacks such as increased hospitalization time and blood loss [12–14]. The pressing challenge, therefore, lies in the quest to enhance the outcomes of LIF surgery. By doing so, we can bridge the gap between fusion and non-fusion surgery, catering to the unique needs of patients who may still require fusion surgery, and offering a more tailored approach that optimizes the surgical outcomes.

As a result, we modified the LIF surgery technique further, to relieve the nerve root axial traction caused by the excessive distraction of intervertebral space to a greater extent [11, 15–18]. Herein we present the study rationale and methodology for this randomized, controlled trial to investigate the clinical outcomes of lumbar surgery sequence of fixation-fusion in LSS patients. It aims to provide more clinical evidence that the modified sequence of the LIF surgery is effective in treating LSS.

## Methods/design

### Study design

The study (http://www.chictr.org.cn/index.aspx ID: ChiCTR2100048507) is a multicenter, randomized, open-label, parallel-group, active-controlled trial that will investigate the clinical outcomes of modified LIF sequence versus conventional LIF sequence in treating patients with lumbar spinal stenosis. It will be conducted following the international Consolidated Standards of Reporting Trials (CONSORT) statement (http://www.consort-statement.org/). Approximately three clinical centers will participate in this study. A brief flow chart of this study is provided in Fig. 1.

**Fig. 1 Fig1:**
[figure not shown]
Study flowchart

### Study patients

A total of 254 eligible patients will be enrolled and randomized after screening at the study sites.

The following are the inclusion criteria:

Age > 18 and < 80 years;Non-pregnant and lactating women;The patient is suffering from lumbar spinal stenosis (refers to the clinical syndrome of the nerve root and cauda equina compression caused by factors such as facet joint hyperplasia and stimulation, which is manifested as low back pain, lower extremity pain, lower extremity numbness, lower extremity weakness, intermittent claudication, and even urine and stool dysfunction);Lumbar spine imaging examination (X-ray film, computed tomography, and magnetic resonance imaging) to diagnose lumbar spinal stenosis, or hyperplasia of facet joint leading to nerve tissue (spinal cord or nerve root) compression, or nerve tissue compression caused by the stenosis of nerve root outlet. On the basis of imaging examination, patients with the Modified Schizas Classification Grade B, C, and D can be enrolled;With significant clinical symptoms of lumbar spinal stenosis, including low back pain, lower limb numbness and pain, and intermittent claudication; On physical examination, the patient had limited lumbar extension, positive or negative straight leg elevation test, and abnormal knee and tendon reflexes;More than 6 months of conservative treatment, no significant improvement of symptoms, seriously affect the quality of life of patients;

Patients with a strong desire to undergo surgery and a full understanding of the differences between the two surgical procedures and their complications signed an informed consent form to voluntarily participate in the clinical trial.

The exclusion criteria are as follows:

Patients with cardiovascular, liver, kidney and hematopoietic systems and other serious primary diseases, mental and malignant diseases such as tumors;Combined with congenital lumbar malformation, past infection history, tumor history, and trauma history, leading to significant abnormal changes in the shape of the lumbar spine;The existence of compression diseases in other parts of the spine other than the lumbar spine, such as cervical disc degeneration, cervical hyperextension, cervical posterior longitudinal ligament ossification, thoracic posterior longitudinal ligament ossification, thoracic ligament yellow ossification, etc.;

There are other diseases such as piriformis syndrome, sciatic nerve injury, polio, and Guillan-Barre syndrome, which affect neurological function and thus interfere with postoperative efficacy.

### Recruitment and randomization process

Before enrollment, there will be one pretreatment screening visit at the study site office, during which each subject will be assigned a unique identification number.

Once considered eligible for entry, the patients with LSS will be randomly assigned to one of two study treatment groups, e.g., either modified LIF sequence or conventional LIF sequence in a 1:1 ratio. A stratified block randomization with randomly varying block size will be used, stratified by surgical segments of lumbar intervertebral disc (single versus multiple segments), modified Schizas classification of LSS (level B versus C/D). Random assignment is generated by an independent statistician and implemented via central randomization mobile phone APP (Shanghai KNOWLANDS MedPharm Consulting Co., Ltd.). In order to avoid potential selection bias, the randomization sequence is concealed from both clinical staff and patients until assignment. With these, neither site investigators nor study participants can influence the study patients’ assigned treatment group.

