**Fig. 2 Fig2:**
[figure not shown]
Representative intraoperative images of modified LIF sequence surgery **A**: The insertion of the pedicle screws; **B**: The installation of the rods prior to the placement of cages; **C**: Direct decompression and insertion of the cage after installation of the rods

All the consumables used in the operation are from the same manufacturer, and the operations will be carried out in strict accordance with a unified standard. The only difference is that patients in the modified LIF sequence group are to be implanted with the fusion cage before with the titanium rod, as opposed to those in the conventional LIF sequence group which are in the opposite order. A detailed description of the LIF surgery technique can be found in previous studies [11, 19].

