### Study visits

Seven study visits per subject will be scheduled in the study as follows: pretreatment visit (Day − 14 to Day 0), treatment visit (Day 1), discharge visit (on the day of discharge from hospital), follow-up visit month 1 (Month 1 post-treatment), follow-up visit month 3 (Month 3 post-treatment), follow-up visit month 6 (Month 6 post-treatment) and follow-up visit month 12 (Month 12 post-treatment). These visits will be made at the patient ward before discharge or study site office after discharge. At scheduled visits, data relating to demography, operation duration, estimated blood loss during operation period, length in days of the stay at hospital, and perioperative complications, visual analogue scale (VAS) pain score and lumbar Japanese Orthopaedic Association (JOA) score, concomitant medication, new-onset adverse events, etc. will be collected. See Fig. 1 for more details.

In case severe adverse events occur, the subjects can decide to drop out any time during the study.

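### Allocation is triggered by eligibility and not tied to the day of surgery, so in this open-label trial the operative plan and pre-surgery withdrawals can depend on the known arm

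*Protocol article*

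**What the plan says.** All references are to the protocol article.

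- **Trigger for allocation.** Recruitment and randomization process: "Once considered eligible for entry, the patients with LSS will be randomly assigned to one of two study treatment groups". Study patients: "A total of 254 eligible patients will be enrolled and randomized after screening at the study sites". Neither section names a day or an operative step.
- **Calendar.** Study visits: "pretreatment visit (Day − 14 to Day 0), treatment visit (Day 1"). The window belongs to the pretreatment visit, and surgery is on Day 1.
- **Masking and concealment.** Study design calls the study a "multicenter, randomized, open-label, parallel-group, active-controlled trial". Under Recruitment and randomization process, "the randomization sequence is concealed from both clinical staff and patients until assignment".
- **Strata.** Randomisation is "stratified by surgical segments of lumbar intervertebral disc (single versus multiple segments), modified Schizas classification of LSS (level B versus C/D").
- **Mechanism.** Allocation is "implemented via central randomization mobile phone APP".
- **Difference between arms.** Description of the interventions says the arms differ only in the order of cage and rod, with the same devices and manufacturer and a uniform operative standard whose content is not given.
- **Analysis set.** Statistical analysis defines the full analysis set (FAS) as patients who were randomised and also had the study operation. They are analysed by assigned group.

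**The concern.** Concealment up to assignment protects who enters the trial. It does not protect what is decided between assignment and the point in the operation where the arms separate. If the surgeon knows the arm in that interval, the comparison may no longer isolate the order of rod and cage.

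Two routes matter:

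1. **Planning.** The number of segments actually operated and the planned extent of decompression should be settled without reference to the arm. If they shift in one arm, their effect on new neurological symptoms is mixed with the effect of sequence. A Cochran-Mantel-Haenszel test stratified on the planned segments, analysed as randomised, does not remove this.
2. **Loss before surgery.** A patient who withdraws, or whose operation is called off, after an unmasked allocation is outside the FAS. If this happens more in one arm, or for different reasons in each arm, the groups analysed are no longer those that randomisation made comparable.

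**Working it through.** **1. The plan's own figure.** Inputs from Sample size calculation: 16% and 5%, two-sided alpha 0.05, power 80%, 1:1. With the pooled-variance formula and mean risk (0.16 + 0.05)/2 = 0.105:

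n per arm = [1.960 × √(2 × 0.105 × 0.895) + 0.842 × √(0.16 × 0.84 + 0.05 × 0.95)]² / 0.11² = 120.7, rounded up to 121, so 242 in total.

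The power at 121 per arm is 80.1%. The total of 254 agrees with 242 × 1.05 = 254.1. The plan's figure reproduces, and the timing of allocation changes none of its inputs.

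**2. What the text permits on timing.** Eligibility triggers allocation, eligibility is assessed at a visit between Day −14 and Day 0, and surgery is on Day 1. The earliest disclosure consistent with this is about two weeks before surgery. The latest is the day of surgery. No sentence narrows the range.

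**3. What is fixed before allocation.** Planned segments (single or multiple) and Schizas grade are strata, so they are declared first. The article does not say that the segments actually operated must match the declared stratum. It does not say that the planned extent of decompression is recorded before allocation.

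**4. Illustration of the planning route.** None of these inputs is in the article: risk 22% with multiple segments, 10% with a single segment, a 50:50 mix, and no true effect of sequence.

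- Average risk: 0.5 × 22% + 0.5 × 10% = 16%.
- Moving 10% of the modified arm from multiple to single: 0.10 × (22% − 10%) = 1.2 points, giving 14.8%.
- Moving 20%: 0.20 × 12% = 2.4 points, giving 13.6%.

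Exact enumeration, 121 per arm, uncorrected chi-square, two-sided 0.05:

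| Conventional v modified | Any rejection | Rejection favouring modified |
|---|---|---|
| 16% v 16% | 5.1% | 2.6% |
| 16% v 14.8% | 5.9% | 4.5% |
| 16% v 13.6% | 8.3% | 7.6% |

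With a 50:50 mix, these shifts mean a changed plan for 0.10/0.5 = 20% and 0.20/0.5 = 40% of multi-segment patients, in one arm only. That is a large change.

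**5. Loss route.** The allowance is 254 − 242 = 12 patients (12/254 = 4.7%). The article does not split these into losses before and after surgery, so this route cannot be sized.

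**6. Where allocation could be placed.** The Fig. 2 caption covers only the modified arm: screws, then "The installation of the rods prior to the placement of cages", then decompression and cage. Relevance and dissemination describes facetectomy and discectomy before the rods. The text after Fig. 2 gives the modified arm's cage and rod order the other way round from both. The conventional arm's full order is left to cited studies. The last step common to both arms cannot be read from the article.

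**The case against.** The strongest reply is that no passage dates randomisation. A reader might infer that patients are randomised at the screening visit, 14 days ahead. The article does not say so: the window is for the visit, randomisation comes after screening, and allocation on the eve or day of surgery fits every sentence. The flowchart, which may show the timing, is not available, and a full protocol exists. This stands as far as it goes, so two weeks is only an outer limit. It does not dispose of the point, because the article does state a trigger, and that trigger is eligibility and not surgery.

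A second reply is that the planned number of segments is a stratum and a uniform standard governs the operation. This narrows the scope for drift. It does not close it, since neither binds what is finally operated as far as the text shows.

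A third is that the illustrated shifts are implausibly large and still small beside the 11-point design difference. That is fair. The figures show direction and mechanism, not an estimate.

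Two further readings go too far. Smaller cages in the modified arm are described as following from the sequence, so they may be part of the intervention and not evidence of bias. A reader of Fig. 2 might also take screw placement as the natural moment for allocation, but the caption describes one arm only and the order of decompression is unsettled.

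Finally, surgeons cannot be masked to the sequence, so choices made after the arms diverge stay open to influence under any timing. That also stands.

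**Conclusion.** The point holds in limited form. The stated trigger, the open-label design, concealment that ends at assignment and an FAS that requires surgery together allow unmasked planning and arm-dependent loss before the operation. Nothing in the article shows that either will occur, or that allocation will in fact be early.

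The size is unknown. A false-positive rate of 5.9% or 8.3% instead of 5.1% rests wholly on assumed risks, mix and shifts. The sample size of 242, or 254 with dropout, is unaffected. This is a cheap improvement to make before recruitment, which had not begun at submission. It is not a flaw that invalidates the design.

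**What to change.** Reword Recruitment and randomization process as follows:

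1. Take consent and confirm eligibility at screening.
2. Record the operative plan (segments to be fused, planned decompression) and enter the strata from that record.
3. Only then request the allocation from the app, on the day of surgery, as late as practicable before the first step at which the arms differ.

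The sponsor should identify that step after reconciling Description of the interventions (Fig. 2 caption and the text after it) with Relevance and dissemination on the order of rods, cage and decompression.

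Most withdrawals before surgery then become losses before randomisation and no longer remove randomised patients from the FAS.

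The cost is protocol wording and one app request on the day of surgery. The arms share devices and consumables, so no extra devices or patients are needed. The downside is that the theatre team must be ready for either order until allocation. Choices after the arms diverge remain unmasked.

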### Description of the interventions

The enrolled subjects will be randomized to undergo LIF surgery with a modified sequence or a conventional sequence. Electromyography serves as a crucial supplementary assessment and prognostic indicator, to minimize the potential bias of the trial data, each participant will undergo electromyography prior to surgery, mitigating the impact of individual patient factors on the prognosis and ensuring the accuracy of the test results. All subjects would be operated on by senior spine surgeons at each site who have at least five years of spine surgical experience and performed more than 100 cases of LIF surgery annually. All subjects will take the same surgical devices. PEEK was uniformly used as the cage material due to practical limitations. Due to practical limitations, the expandable cage was not used in this clinical trial. Therefore, only static cage is used uniformly for all patients. Representative intraoperative images of modified LIF sequence surgery is provided in Fig. 2.

**Fig. 2 Fig2:**
[figure not shown]
Representative intraoperative images of modified LIF sequence surgery **A**: The insertion of the pedicle screws; **B**: The installation of the rods prior to the placement of cages; **C**: Direct decompression and insertion of the cage after installation of the rods

All the consumables used in the operation are from the same manufacturer, and the operations will be carried out in strict accordance with a unified standard. The only difference is that patients in the modified LIF sequence group are to be implanted with the fusion cage before with the titanium rod, as opposed to those in the conventional LIF sequence group which are in the opposite order. A detailed description of the LIF surgery technique can be found in previous studies [11, 19].

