#### Relevance and dissemination

Our retrospective data (2020) [11] revealed that the modified sequence of LIF surgery can significantly reduce the incidence of immediate post-operative symptoms for patients with single-level lumbar disc herniation via installation of rods prior to insertion of the cage. For the purpose of a higher level of evidence, herein it is expected that this multicentre randomized controlled trial will clearly demonstrate the two types of surgery sequence in terms of immediate post-operative symptoms among diverse LSS patients. It is well known that the adverse experience will significantly compromise the quality of patients’ lives and sometimes even require revision surgery [11, 23, 24].

In the RCT, the conventional LIF surgery sequence will be changed in order: the intervertebral space is first restored and maintained without any distraction or compression force after facetectomy and discectomy; then, differently, the installing and tightening of rods are to be performed prior to the insertion of the cages. By this modified sequence, the inserted cage would be usually smaller than that in the conventional one. In addition, the modified procedure would make it easier to insert an appropriately small cage and even avoid smaller cage to insert.

Given that the immediate postoperative symptoms are available soon after surgery, the study is designed short (approximately three months per subject) in follow-up time. However, it makes sure that we can follow up study patients well and obtain higher quality of data. As regards data analysis, in order to control any possible biases resulting from imbalanced confounders among patients, we will then use stratified randomization technique as is appropriate for this study. This had better help set up any statistical modeling for data analysis. A dedicated data management and analysis team is in place for this study.

In summary, the modified LIF surgery sequence with a rod-prior-to-cage order might be considered more reasonable in treating patients with lumbar spinal stenosis. The study findings will be shared with participating hospitals, and the academic community to promote the clinical management of immediate post-operative symptoms after LIF surgery.

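### The sentence that defines the only difference between the arms gives the modified group cage before rod, the reverse of the order stated for that arm everywhere else in the article

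*Protocol article*

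**What the plan says.** Under Description of the interventions, the text after Fig. 2 states that consumables come from one manufacturer and that a single operating standard applies. It then gives the sole difference between the arms: "patients in the modified LIF sequence group are to be implanted with the fusion cage before with the titanium rod". The same sentence goes on to fix the other arm as the reverse, with the words "as opposed to those in the conventional LIF sequence group which are in the opposite order". As written, modified means cage then rod, and conventional means rod then cage.

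The Fig. 2 caption, presented as images of the modified sequence, says for panel B "The installation of the rods prior to the placement of cages" and for panel C "Direct decompression and insertion of the cage after installation of the rods".

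Relevance and dissemination describes the modified sequence three times:
- for the earlier data, "via installation of rods prior to insertion of the cage";
- for this trial, "the installing and tightening of rods are to be performed prior to the insertion of the cages";
- in the summary, "the modified LIF surgery sequence with a rod-prior-to-cage order".

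The Abstract conclusion and the last paragraph of the Introduction call the modified technique the fixation-fusion sequence. The Introduction also describes the earlier work as fixation followed by fusion implantation.

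**The concern.** Surgeons' qualifications, devices, cage material and consumables are the same in both arms, so the order of rod and cage is the whole of the randomised intervention. The one sentence that sets out this contrast for both arms conflicts with the rest of the article. It cannot be read as loose wording about one arm, because it fixes the other arm as the reverse.

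Two parts of the analysis depend on the definition:
- **Direction of the hypothesis.** Sample size calculation aims to show the modified sequence superior, with 16% events in the conventional arm and 5% in the modified arm. It takes these rates from the earlier study, which Relevance and dissemination describes as rod first.
- **Safety set.** Statistical analysis groups these patients by the operation they actually had. With two opposite definitions of each operation in one document, that grouping is ambiguous.

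**Working it through.** **1. Statements side by side**

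| Place | Order given for the modified sequence |
|---|---|
| Description of the interventions, sentence after Fig. 2 | cage, then rod |
| Fig. 2 caption, panel B | rod, then cage |
| Fig. 2 caption, panel C | rod, then cage |
| Relevance and dissemination, earlier data | rod, then cage |
| Relevance and dissemination, this trial | rod, then cage |
| Relevance and dissemination, summary | rod, then cage |
| Abstract, Conclusion | fixation, then fusion |
| Introduction, earlier study | fixation, then fusion |
| Introduction, last paragraph | fixation, then fusion |

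The last three rows count as rod first if fixation means the rod and fusion means the cage, which is how the article uses the terms. The first five rod-first rows need no such reading. One statement stands against eight, and the one is the arm definition.

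**2. The plan's own sample size**

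Inputs from Sample size calculation: p1 = 0.16, p2 = 0.05, two-sided alpha 0.05, power 80%, 1:1 allocation. The mean rate is (0.16 + 0.05)/2 = 0.105.

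n per arm = [1.960 × √(2 × 0.105 × 0.895) + 0.842 × √(0.16 × 0.84 + 0.05 × 0.95)]² / 0.11²
= [0.850 + 0.359]² / 0.0121 ≈ 121

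The total is 2 × 121 = 242, as stated, with power 80.1%. Dividing by 0.95 gives 254.7, so the stated 254 agrees to within one patient.

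**3. Effect of exchanging the procedures**

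The formula is symmetric in the two rates, so the total stays at 242. The direction does not. Suppose the arm labelled modified received the procedure assumed to give 16%, and the arm labelled conventional the one assumed to give 5%. With 121 per arm:
- the chance of a significant result favouring the label conventional is about 80%;
- the chance of one favouring the label modified is below 0.0001%.

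**4. Hypothetical partial exchange**

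Let f be the share of patients treated at centres that follow the sentence literally. The planned difference, modified minus conventional, is 5 − 16 = −11 points, and it becomes +11 at those centres. The expected overall difference is (1 − f)(−11) + f(+11) = −11(1 − 2f).

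| f | Expected difference (points) |
|---|---|
| 0 | −11 |
| 1/3 (one of three equal centres) | (2/3)(−11) + (1/3)(+11) = −3.7 |
| 1 | +11 |

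The article gives no value for f and no centre sizes, and says only that about three centres will take part. The table shows a range and is not a forecast.

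**The case against.** The strongest reply is that this is a drafting slip with no practical effect. Every other statement agrees, and the caption beside the sentence shows the modified sequence panel by panel. Surgeons must perform more than 100 of these operations a year. The article also refers to a separate approved protocol (version 1.0), to a unified operating standard and to earlier publications for the detailed technique, none of which is shown here. Most of this stands. It makes an actual exchange of procedures unlikely, but it does not remove the contradiction from the sentence that defines the trial's contrast.

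A reader might infer three stronger things, and the article supports none of them:
- **That sites would give patients the other arm's operation.** This assumes they work from one sentence of a journal article. The documents that govern the surgery are not shown, so the −3.7 and +11 figures remain illustrations.
- **That the safety set would be coded the wrong way round.** Nothing says that surgery received is coded from the arm name. The supported statement is that the definition is ambiguous.
- **That the position of decompression is a second contradiction.** Panel C reads "Direct decompression and insertion of the cage after installation of the rods", while Relevance and dissemination has the disc space held "without any distraction or compression force after facetectomy and discectomy" and the rods installed next. The article never equates direct decompression with facetectomy and discectomy, and in panel C the final phrase may qualify only the cage insertion. This is an ambiguity to clear up.

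**Conclusion.** The contradiction is real, sits in the current text and must be corrected, because the order of rod and cage is the only stated difference between the arms. As written, the sentence exchanges the arms, reverses the meaning of the 16% versus 5% hypothesis and makes grouping by surgery received ambiguous. The sample size is unaffected: 242 reproduces and is the same with the rates exchanged.

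The established fault is in the definition. Harm to the trial's result is conditional on some site following the sentence: from no effect if none does, through 3.7 points if one of three equal centres does, to a change of sign if all do. These figures assume the planned rates and complete reversal at the centres concerned. No view is taken here on which surgical order is right.

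**What to change.** - Reconcile the arm-defining sentence under Description of the interventions with the Fig. 2 caption, the Abstract, the Introduction and Relevance and dissemination, so that one rod/cage order per arm is stated throughout.
- Check that the approved protocol and the operative instructions held at the sites carry the same wording.
- Define surgery received, for the safety set, by the rod/cage order recorded for each patient.
- As a secondary clarification, state where decompression falls relative to rod installation, since panel C and Relevance and dissemination can be read differently.

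The cost is a wording correction, with no added patients or procedures. Trial status reports that recruitment had not begun at submission. If it has begun since, the recorded orders of the patients already operated on should also be checked against their assigned arm.
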